**0. Overview.**

**0.1. objectives**

　To test the non-inferiority of intravenous patient-controlled analgesia (iv-PCA) as postoperative analgesia to epidural analgesia (EDA) with respect to post-operative analgesia in patients aged 20 years and older undergoing laparoscopic gastrectomy for gastric cancer.

● Primary endpoint

　　　　　　Pain score using Numerical Rating Scale (NRS) at rest 24 hours after surgery.

　　● Secondary endpoints

　　　　　　Days to achieve discharge criteria*, Duration of postoperative hospital stay, Incidence of postoperative complications, Pain score (NRS) on postoperative days 2, 3 and 4 at rest, Additional analgesic usage, Analgesic method-related complications.

*Discharge criteria: (1) Good pain control with oral analgesics (2) Able to walk on own (3) Consume more than half of meal (4) No post-operative complications, or as far as possible treated on an outpatient basis.

● Safety assessment.

　　　　　　Frequency of analgesia-related adverse events.

**0.2. subject.**

　Inclusion criteria.

1) Patients with gastric cancer which has been diagnosed histologically and scheduled to undergo laparoscopic gastrectomy (total gastrectomy, distal gastrectomy or proximal gastrectomy).

　　　2) Patients aged between 20 and 80 years

　　　3) Patients who can provide written informed consent

　Exclusion criteria.

1) Patients with a preoperative ASA-PS (American Society of Anesthesiologists Physical Status) of 4 or higher

　　　2) Patients undergoing anticoagulant therapy

　　　3) Medical contraindication for EDA

4) Abnormal anatomy of the spinal column

5) Patients undergoing neoadjuvant chemotherapy

6) Patients with immunodeficiency

7) Patients undergoing palliative surgery

8) Patients undergoing emergency surgery

　　　9) Otherwise judged by the investigator as unsuitable for enrollment

**0.3. analgesic methods**

　　　Epidural analgesia (EDA: Epidural Analgesia).

　　　　0.2% ropivacaine + fentanyl (1 µg/mL) continuous, 2-6 ml/hr, bolus 3 ml, 15 min intervals

　　　Intravenous-patient-controlled analgesia 　　　(iv-PCA: intravenous patient-controlled analgesia).

　　　　Fentanyl (10 µg/mL) continuous, 0-2 ml/h, 1-2 ml bolus, 15 min intervals, max 4 doses/hr

**0.4. expected enrolment and study duration**

　　　Expected number of patients enrolled: 132 (66 in each group)

　　　Registration period : 3 years and 6 months (from 1 July 2017 to 31 December 2020)

　　　Analysis period. : 6 months.

　　　Total study period : 4 years (from 1 July 2017 to 30 June 2021)

**1. background**

**epidural analgesia as postoperative analgesia**

　　　In abdominal surgery, epidural anaesthesia, used intraoperatively alone or in combination with general anaesthesia, has been reported to have many benefits in terms of intraoperative management. It has also been reported to have many advantages in postoperative analgesia, such as reducing postoperative respiratory complications and preventing the occurrence of ileus and has been established as an essential method of analgesia in abdominal surgery.

　　　On the other hand, however, epidural analgesia may carry the risk of serious complications such as hematomas, abscesses, and nerve damage. The frequency of serious complications is considered to be extremely rare and has been reported to be around 1 in 150,000 to 190,000 cases. Various biases have been shown to play a significant role in their frequency, and the choice of epidural analgesia should be considered the risks from multiple perspectives.

**increased use of laparoscopic surgery for gastric cancer**

In recent years, laparoscopic surgery has become increasingly popular in abdominal surgery. In gastric cancer surgery, a 2013 national survey by the Japanese Society for Endoscopic Surgery revealed that more than 42% of gastric cancer operations were performed laparoscopically, and the proportion is increasing. The minimally invasive nature of laparoscopic surgery compared to open surgery has been reported in many cases, showing its superiority in terms of cosmetics, reduced wound pain, enhanced postoperative respiratory function, reduced postoperative hospital stay and early recovery.

**epidural analgesia for laparoscopic colorectal resection**

　　　The Enhanced recovery after surgery (ERAS) protocol is a multidisciplinary treatment programme that aims to achieve rapid recovery after highly invasive surgery by integrating a range of evidence-based treatments to help accelerate recovery after surgery. ERAS protocols have been proven to reduce postoperative complications, hospital stays and healthcare costs after colorectal resection. Within the ERAS protocols, fluid management, minimally invasive surgery and epidural analgesia are considered. However, the effectiveness of epidural analgesia is debatable in minimally invasive surgery such as laparoscopic colorectal surgery, with recent reports suggesting that epidural analgesia may even delay postoperative recovery. The ERAS Group guidelines also state that epidural analgesia and patient-controlled analgesia (PCA) are equivalent in laparoscopic colorectal resection.

**subject.**

　　　The incidence of gastric cancer, the subject of this study (2011 statistics), is still the leading malignant neoplasm in Japan, ranking first among men and third among women, and surgery is the first choice for the treatment of resectable lesions. Intraoperative and postoperative analgesia for gastric cancer surgery, including laparoscopic surgery, is currently the standard method of analgesia, unless epidural analgesia is contraindicated, such as when anticoagulants are being administered.

**significance**

　　　Epidural analgesia is now routinely used in intra- and postoperative analgesia for abdominal surgery and has proven useful as postoperative analgesia. However, epidural analgesia may be associated with the risk of serious complications such as haematoma, abscess and nerve damage. Furthermore, adverse events such as postoperative hypotension and urinary retention have also been reported with epidural analgesia, which, while effective for pain relief, may lead to delayed postoperative mobilizaion and may not lead to a true early postoperative recovery.

　　　Furthermore, recent advances in echo-guided peripheral nerve blocks other than epidural analgesia, intravenous patient-controlled analgesia (iv-PCA) and multimodal analgesia (a combination of various analgesia), in addition to the widespread use of laparoscopic surgery for gastric cancer, have made the need for epidural analgesia for epidural analgesia is debatable. If iv-PCA proves to be non-inferior to epidural analgesia (EDA) in postoperative pain relief for laparoscopic gastrectomy, it could provide safer and simpler postoperative analgesia and reduce the burden and healthcare costs for gastric cancer surgery patients.

**2. research methods**

**types and designs of research**

　　　Prospective randomised controlled clinical trial of early recovery with postoperative epidural analgesia (EDA) versus patient-controlled analgesia (iv-PCA) in patients undergoing laparoscopic gastrectomy for gastric cancer.

**the expected duration of the research subject's participation in the study**

The period of study participation is from the time consent is obtained in the preoperative period until discharge from hospital after surgery.

**Intervention**

Use epidural analgesia (EDA) or patient-controlled analgesia (iv-PCA) as postoperative analgesia. Dosages are equivalent to those in routine practice.

● Epidural analgesia (EDA)

A catheter is inserted into the thoracic spine (Th8-Th10) epidural space before general anaesthesia and 0.2% ropivacaine + fentanyl (1 µg/mL) is administered continuously, 2-6 ml/hr, 3 ml bolus, every 15 min, starting postoperatively, in principle until the second postoperative day, but can be continued until the seventh postoperative day if the pain management team considers it advisable.

● Intravenous patient-controlled Analgesia (iv-PCA)

　　Fentanyl (10 µg/mL) administered intravenously continuously (0-2 ml/h, 1-2 ml bolus, 15 min intervals, max 4 doses/h) from postoperative period, in principle until the second postoperative day, but can be continued until the seventh postoperative day if the pain management team considers it advisable.

**equipment and materials used for the intervention.**

　　　Use epidural catheter kit for epidural catheter insertion.

　　　Use 0.2% ropivacaine (Anapain®) and fentanyl injection as epidural drugs.

　　　Fentanyl injection solution is used for intravenous patient-controlled analgesia.

　　　Both epidural and patient-controlled analgesia are administered using a PCA pump.

**provisions on concomitant medications.**

　　　Concomitant medications: acetaminophen (Acerio®) Used as additional analgesia in cases of poor pain relief (NRS≥3) during postoperative epidural analgesia or patient -controlled analgesia, 1000 mg per dose over 15 minutes with a minimum interval of 4 hours between doses. However, it should not be administered to patients with contraindications to paracetamol administration. For patients weighing less than 50 kg, a maximum dose of 15 mg per kg of body weight should be administered. Mainly used up to the third postoperative day before oral intake is started.

　　　　　　　Celecoxib (Celecox®) Two tablets (200 mg) twice daily, after breakfast and dinner, with oral intake starting on the third postoperative day, to be continued until the day of discharge. It can be discontinued before discharge if the patient wishes to discontinue and is not administered to patients with contraindications to celecoxib administration.

　　　　　　　Flurbiprofen (Ropion®) Additional analgesia in case of poor pain (NRS≥3) with postoperative epidural analgesia or patient-controlled analgesia 50 mg per dose diluted in 100 ml of saline and administered over 30 minutes with a minimum interval of 4 hours between doses. It is mainly used up to the third postoperative day before oral intake is started.

　　　　　　　Loxoprofen (Loxonin®) From postoperative day 3 after oral intake has started, as an additional analgesic in case of poor pain relief (NRS≥3) with epidural or patient-controlled analgesia One tablet (60 mg) should be taken orally at least 4 hours between doses.

　　　　　　　Pentazocine (Sosegon®) Used as additional analgesia in cases of poor pain relief (NRS≥3) with postoperative epidural analgesia or patient-controlled analgesia; 15 mg per dose diluted in 100 ml of saline and administered over 30 minutes with a minimum interval of 4 hours between doses. Mainly used up to the third postoperative day before oral intake is started.

**methods of cessation (withdrawal)**

If neurological symptoms or pain or swelling at the site of epidural catheter insertion (see Adverse events for definitions) are observed, the epidural analgesia should be discontinued. Epidural analgesia should also be discontinued if self-extraction of the epidural catheter by the patient occurs postoperatively. Both epidural analgesia and patient-controlled analgesia should be discontinued if adverse events such as nausea caused by fentanyl are difficult to control.

**research subject guidance information**

　　　Patients are instructed in the use of the PCA and PCEA pumps by the anaesthetist in charge and the nurse in charge in the post-operative recovery room and after returning to the ward.

**case registration and allocation methods**

How to enrol research subjects: the principal investigator or research associate 1) obtains written consent; 2) The date consent was obtained and the information necessary to correspond the subject to the subject identification code should be noted on the list of subject identification codes kept by the principal investigator; 3) Submit the case registration form with the subject identification code to the research office 4) Receive confirmation of eligibility and a registration confirmation form with the subject registration number and the analgesic method assigned. 5) Report promptly when there is withdrawal of consent, discontinuation, drop-out, etc.

　Method of allocation of study subjects: allocation of study subjects to each treatment group is performed by the dedicated data manager. The subjects will be allocated to each treatment group in the order of case registration according to a pre-designed allocation list using the stratified substitution block method, and a confirmation of registration will be issued, indicating the subject registration number and the name of the treatment group. The allocation table is kept by the secretariat.

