**4. Evaluation items**

　　　● Primary endpoint

　　　　　　Pain score using Numerical Rating Scale (NRS) at rest 24 hours after surgery.

　　 ● Secondary endpoints

　　　　　　Days to achieve discharge criteria*, Duration of postoperative hospital stay, Incidence of postoperative complications, Pain score (NRS) on postoperative days 2, 3 and 4 at rest, Additional analgesic usage, Analgesic method-related complications.

*Discharge criteria: (1) Good pain control with oral analgesics (2) Able to walk on own (3) Consume more than half of meal (4) No post-operative complications, or as far as possible treated on an outpatient basis.

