**statistical analysis methods**

　　　After enrolment in the study, patients who did not withdraw their consent and for whom protocol treatment was administered will be included in the analysis population (Full analysis set, FAS). For the analysis of the primary endpoint, NRS at 24hrs after surgery of the EDA and iv-PCA groups will be calculated for the FAS and analysed by Student t-test. Secondary endpoints will be analysed by the X^2^ test was employed to analyze categorical variables. Welch’s t test was used to compare continuous variables.

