**6. Target case numbers and rationale for setting them**

[Target number of cases] 132 cases

[Rationale for setting up the case number].

In a retrospective study of patients who underwent laparoscopic gastrectomy for gastric cancer at our hospital and who received postoperative pain management with EDA or iv-PCA, respectively, the mean 24-hour postoperative pain score (NRS) was 2.11 and standard deviation 1.9 in the EDA group, and in the iv-PCA group the mean 2.36 with a standard deviation of 1.8.

Since only patients who meet the inclusion criteria and do not meet the exclusion criteria will be included in this study, it is assumed that the variation in scores will be smaller than in the existing data, as the patients will be more similar than in the existing data. Therefore, in the caseload design of this study, it is assumed that the standard deviation will be about 10% smaller, with a mean of 2.11 and a standard deviation of 1.71 for the EDA group and a mean of 2.36 and a standard deviation of 1.62 for the iv-PCA group.

Assuming a non-inferiority margin of 1 and a sample size of α = 0.05 and β = 0.2, the sample size is 62 cases in one group (124 cases in both groups). Assuming a drop-out rate of approximately 5%, the target number of cases is 132 in both groups.

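### Allocation is stratified but the primary t-test ignores the strata: valid and adequately powered as planned, but conservative to the extent that the strata predict 24-hour pain

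*Protocol*

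**What the plan says.** Section 2 of the protocol (case registration and allocation methods) states that patients are assigned in order of registration "according to a pre-designed allocation list using the stratified substitution block method". It does not name the stratification factors, the number of strata or the block size.

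The primary endpoint in section 4 is "Pain score using Numerical Rating Scale (NRS) at rest 24 hours after surgery". Section 5 (statistical analysis methods) fixes its analysis: "NRS at 24hrs after surgery of the EDA and iv-PCA groups will be calculated for the FAS and analysed by Student t-test". Neither that section nor any other provides for a stratified or covariate-adjusted comparison.

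Section 6 sizes the trial from whole-arm means and SDs. For the iv-PCA arm it assumes 2.36 and 1.62; the epidural arm enters "with a mean of 2.11 and a standard deviation of 1.71 for the EDA group". The design criterion is "Assuming a non-inferiority margin of 1 and a sample size of α = 0.05 and β = 0.2", and this leads to 62 evaluable patients per arm, 124 in all. After the allowance for drop-out the target is 132.

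**The concern.** Stratified blocking keeps the arms nearly equal in size within each stratum. Differences in mean pain between strata then largely cancel from the treatment difference, so its true sampling error reflects only the variation within strata. A two-sample t-test estimates the error from the total variation within each arm, which still includes the differences between strata. If the strata are prognostic, the reported standard error is too large.

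Non-inferiority here turns on where a confidence limit falls relative to 1 NRS point, so interval width matters directly. An analysis that ignores prognostic strata gives up precision that the randomisation has already secured.

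**Working it through.** **Inputs from section 6.** SDs 1.71 (EDA) and 1.62 (iv-PCA); means 2.11 and 2.36, so an assumed true difference of 0.25; margin 1; 62 evaluable per arm; power 80%. The sidedness of α = 0.05 is not stated.

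**Step 1: reproduce the plan's figure.**
- Common SD = √[(1.71² + 1.62²)/2] = 1.666.
- Distance from the assumed difference to the margin = 1 − 0.25 = 0.75.
- Normal approximation, one-sided 5%: n = 2 × [1.666 × (1.645 + 0.842)/0.75]² ≈ 61 per arm. The noncentral-t calculation gives 62, as stated.
- At one-sided 2.5% the same calculations give 78 and 79. The stated 62 therefore rests on one-sided 5%, and the results below use that level.
- Unadjusted standard error at 62 per arm = 1.666 × √(2/62) = 0.299. Power of the t-test with 122 degrees of freedom = 80.2%. The planned 80% is thus already the power of the unadjusted test.

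**Step 2: allow the strata to explain a share R² of NRS variance.** The protocol gives no R², so 0 to 15% is assumed. Arms are taken as equal within strata, and four strata are assumed for the degrees of freedom (119 in the adjusted model; the number of strata hardly affects the result).
- True standard error of the difference, which the adjusted model estimates: 0.299 × √(1 − R²).
- Excess width of the unadjusted interval: 1/√(1 − R²) − 1.
- Power of the unadjusted test: Φ[(0.75 − 1.657 × 0.299)/true SE], where 1.657 is the one-sided 5% t quantile on 122 degrees of freedom.
- Power of the adjusted test: noncentral t with noncentrality 0.75/true SE.
- Actual size of the unadjusted test: approximately Φ[−1.645/√(1 − R²)].

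| Assumed R² | True SE | Interval too wide by | Power, unadjusted | Power, adjusted | Gain (points) | Actual size of unadjusted test |
|---|---|---|---|---|---|---|
| 0% | 0.299 | 0% | 80.2% | 80.2% | 0 | 5.0% |
| 5% | 0.292 | 2.6% | 80.8% | 81.9% | 1.1 | 4.6% |
| 10% | 0.284 | 5.4% | 81.5% | 83.7% | 2.2 | 4.2% |
| 15% | 0.276 | 8.5% | 82.2% | 85.5% | 3.4 | 3.7% |

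Example at R² = 10%: true SE = 0.299 × √0.90 = 0.284; excess width = 1/√0.90 − 1 = 5.4%; unadjusted power = Φ[(0.75 − 0.496)/0.284] = 81.5%.

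Gains are computed before rounding. The half-width of the unadjusted 90% interval is 0.496 throughout; the adjusted one is 0.496, 0.483, 0.470 and 0.457 in the four rows.

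**The case against.** The strongest reply is that nothing is broken. The sample size was computed from total SDs for the unadjusted test, so the plan reaches its target. If the strata are prognostic, the t-test's true power rises slightly above 80.2%. The treatment estimate stays unbiased, and the error is on the safe side: a conservative test does not raise the risk of a false claim of non-inferiority. All of this stands.

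A reader might infer that the trial loses part of its planned 80%, or that its interval is bound to be too wide. The documents support neither. The loss is conditional on strata the protocol does not identify, and no section links any baseline factor to NRS. If the strata do not predict pain, the loss is nil. A reader might also set the adjusted power of 82–86% against the planned 80% and infer a gain of 2 to 6 points. That compares two different values of R². At the same R² the gain is 1.1 to 3.4 points.

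Two further objections carry less weight. Covariate adjustment is often left to a statistical analysis plan, but here the protocol itself names the primary test. The name of the block method reads like a translation, but the text does say that the allocation is stratified. If it is not, that sentence needs correcting instead.

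**Conclusion.** The mismatch between stratified allocation and an unadjusted primary test is real and worth correcting, but it concerns efficiency and not validity. Type I error is not inflated and the planned power is met.

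What is forgone is extra precision: 0 to 8.5% of interval width and about 0 to 3.4 points of power for R² between 0 and 15%. These figures rest on one-sided 5%, 62 evaluable per arm, the section 6 SDs and near-equal arms within strata. The direction is certain if the strata are prognostic; the size cannot be fixed from the protocol.

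**What to change.** In section 2, name the stratification factors of the allocation list. In section 5, make the primary analysis a linear model of 24-hour resting NRS on arm plus those factors, and compare the confidence limit of the adjusted difference (iv-PCA minus EDA) with the margin of 1. Keep the unadjusted t-test as a sensitivity analysis.

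The cost is a short amendment to two sections. Each patient's stratum must be known at registration for the list to be used, so no new data and no additional patients are needed. The statistical price is a few of the 122 degrees of freedom: even with strata that explain nothing, power stays at 80.2% to one decimal place.

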**actions to be taken after the completion of the research.**

After the completion of this study, the doctor in charge will provide the medical care he or she considers most appropriate for the study subjects, including the results obtained in this study.

**3. Observations and laboratory tests**

**pre-registration assessment items (pre-operative)**

1) Medical history interview:

　　　　　History of spinal compression fractures

　　　　　On anticoagulant/antiplatelet drugs

　　　　　Presence or absence of back infection.

　　　　　General condition: PS(ECOG), ASA

Age.

　　　　　Height, weight.

　　　　　Respiratory failure.

　　　　　Cancer Chemotherapy

　　　　　Severe infections.

　　　　　Drug allergy.

　　　　　co-morbidities

　　　2) 12-lead ECG at rest

　　　3) Respiratory function tests: %VC, FEV 1.0%.

　　　4) Blood tests: white blood cells, red blood cells, haemoglobin, platelets

　　　5) Biochemical tests: albumin, total bilirubin, AST, ALT, BUN, creatinine

　　　6) Coagulation tests: PT, APTT, D-dimer

　　　7) Simple chest X-ray

　　　8) CT scan of the abdominopelvic region (simple CT is acceptable if contrast-enhanced CT is not possible due to contrast allergy).

　　　9) Upper gastrointestinal endoscopy (with diagnosis of gastric cancer on histopathological examination)

**surgical and tumour endpoints**

　　　1) Surgical technique (resection method, reconstruction method, degree of lymph node dissection, presence or absence of complications of resected organs).

2) Surgical time

　　　3) Blood loss and transfusion volume

　　　4) Pathological findings of the tumour (histological type, wall depth, lymph node metastasis, histological progression and overall radiculopathy)

**post-operative endpoints (until discharge)**

Basically, it conforms to the post-operative clinical pathway for gastric cancer currently in use at the hospital.

　　　1) Check vital signs: blood pressure, pulse, temperature, oxygen saturation

　　　2) Blood tests (postoperative days 1, 3 or 4 and 7)

White blood cells, red blood cells, haemoglobin, platelets

　　　3) Biochemical tests (postoperative days 1, 3 or 4 and 7)

Albumin, total bilirubin, AST, ALT, BUN, creatinine, CRP

　　　4) Coagulation test (postoperative day 7)

PT, APTT, D-dimer.

　　　5) Pain assessment

Pain scores at rest and during body movement are assessed twice daily according to the Numerical Rating Scale: NRS.

　　　6) Additional analgesic usage

　　　　　　Additional analgesic

　　　7) Patient satisfaction.

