**post-operative endpoints (one month after discharge)**

　　　Interview and examine the patient for the development of analgesia-related adverse events at the time of the outpatient visit.

　　　If it is difficult to come to the hospital within one month after surgery, it is acceptable to come to the hospital within three months after surgery.

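### Four of the five analgesia-related event groups that the protocol names have no listed in-hospital observation, and the discontinuation rule for epidural analgesia cites definitions that are not there

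*Protocol*

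**What the plan says.** Safety is an endpoint twice over. Section 0.1 sets the safety assessment as "Frequency of analgesia-related adverse events", and section 4 ends its list of secondary endpoints with "Additional analgesic usage, Analgesic method-related complications".

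The protocol also says which events it has in mind. The significance part of section 1 states that "adverse events such as postoperative hypotension and urinary retention have also been reported with epidural analgesia", and section 9 repeats this. Under methods of cessation (section 2), the epidural rule begins "If neurological symptoms or pain or swelling at the site of epidural catheter insertion (see Adverse events for definitions) are observed", and both methods are to be discontinued if "adverse events such as nausea caused by fentanyl are difficult to control".

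For the hospital stay, section 3 has seven numbered items: vital signs, three groups of laboratory tests, pain scores twice a day, additional analgesic use, and patient satisfaction. The first reads "Check vital signs: blood pressure, pulse, temperature, oxygen saturation". The list is introduced by a statement that care broadly follows the hospital's existing clinical pathway.

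After discharge there is one visit: "Interview and examine the patient for the development of analgesia-related adverse events at the time of the outpatient visit". Its heading places it one month after discharge, and the text allows it up to three months after surgery.

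**The concern.** The argument for iv-PCA in sections 1 and 9 is that it may be safer than epidural analgesia if it relieves pain about as well. The comparison of common side effects therefore carries part of the conclusion. That comparison is only as good as the way events are found.

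Urinary retention and nausea are short-lived, and analgesia runs in principle to the second postoperative day and at most to the seventh (section 2, Intervention). An interview weeks later is a weak instrument for counting them. If, during the stay, events reach the database mainly when someone happens to notice and report one, counts will tend to be low. They may also be unequally low, because staff who can see which technique a patient has may look harder for its known effects.

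The discontinuation rule raises a separate matter. It rests on signs whose meaning is said to be given elsewhere. If that text is missing, different clinicians have no common wording to apply.

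**Working it through.** The plan gives no figure on this point, so the check sets the passages side by side.

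**Step 1. Named events against listed in-hospital observations (section 3, until discharge).**

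| Event group | Where named | Listed in-hospital item |
| --- | --- | --- |
| Hypotension | Sections 1 and 9 | Blood pressure; no frequency or threshold |
| Urinary retention | Sections 1 and 9 | None |
| Nausea | Section 2, cessation | None |
| Neurological symptoms | Section 2, cessation | None |
| Catheter-site pain or swelling | Section 2, cessation | None |

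One of five has a listed observation; four of five have none. The laboratory items do bear on safety in general, since section 3 counts abnormal laboratory values as adverse events, but they do not address these four.

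**Step 2. How an in-hospital event reaches the database.** Section 5 (data aggregation) has an adverse event form, sent when an event occurs. Section 12 requires the physician to document an event in the medical record and on that form once it is observed. Severity grading by CTCAE v4.0 and committee assessment of severity and causality (section 3) work on events already recorded. All of these begin with someone noticing. Section 5 also lists a case record form for the hospital stay, whose fields are not shown.

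**Step 3. The scheduled enquiry.** The outpatient visit is the only point at which the protocol says that patients are asked about analgesia-related events. Section 2 states that participation lasts until discharge, so this visit falls outside the stated participation period. Section 5 lists no form for it, so the listed forms do not show how a visit with no events would be recorded.

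**Step 4. The cross-reference.** The epidural rule in section 2 says "see Adverse events for definitions) are observed, the epidural analgesia should be discontinued". The adverse-event text in section 3 defines an adverse event, a side effect and a serious event, names the severity scale, and sets causality categories. It defines neither neurological symptoms nor catheter-site pain or swelling.

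**Step 5. What unequal recording would do (assumed values, for scale only).** Suppose the true event rate *r* is the same in both arms and the proportions recorded are *s*₁ and *s*₂. The apparent difference is *r* × (*s*₁ − *s*₂).

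- *r* = 10%, recording 90% against 60%: 0.10 × 0.30 = 3 percentage points, or 0.03 × 66 ≈ 2 patients per arm.
- *r* = 20%, same recording: 0.20 × 0.30 = 6 points, or 0.06 × 66 ≈ 4 patients.
- *r* = 30%, recording 90% against 45%: 0.30 × 0.45 = 13.5 points, or 0.135 × 66 ≈ 9 patients.

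The 66 per arm is from section 0.4; every rate is an assumption. Swapping *s*₁ and *s*₂ reverses the sign, so the sum says nothing about which arm would look better.

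**The case against.** The strongest reply is that a short list in a protocol is not the whole of data collection. The list in section 3 defers to a clinical pathway that may contain nursing checks for nausea, voiding and the catheter site. The case record form for the stay may have fields for them, and a pain management team is involved in both arms. The list also has no line for postoperative complications or for the discharge criteria, both of which underlie secondary endpoints, so absence from it does not prove that something goes uncollected. The outpatient visit can be read as an addition aimed at late effects such as abscess or nerve damage.

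Most of this stands, and it limits what can be claimed. A reader might infer four stronger things that the documents do not support:

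- *That no named event is checked in hospital.* Blood pressure is listed, so hypotension has an observation.
- *That the safety endpoint is shown to rest on unprompted reporting in an open trial.* The form and the pathway are not shown. The protocol nowhere calls the trial open; that is an inference from a catheter in one arm only and the absence of any masking text.
- *That iv-PCA would gain a false safety advantage of a given size.* The rates are assumed, and the direction is not determined. The cessation text itself ties nausea to fentanyl, which could lead staff to look harder for it under iv-PCA.
- *That epidural analgesia will be stopped late in some patients and for trivial signs in others.* Nothing in the text shows this.

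What the reply does not remove is that the written rules act only after an event is noticed, and that nothing says pathway checks are recorded as trial data in the same way in both arms. Nor does it touch the missing definitions. CTCAE is invoked there to grade severity, and the section itself still gives no definition of the signs the rule relies on.

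**Conclusion.** The point holds as an inexpensive improvement together with passages to reconcile. For four of the five event groups that the protocol names, it lists no in-hospital observation; for the fifth it lists blood pressure without frequency or threshold. The one scheduled enquiry comes after discharge, when participation has by the protocol's own statement ended. Recording could therefore differ between arms, in either direction, by an amount the documents do not allow to be estimated. The 3 to 13.5 points worked out above only illustrate what the assumed rates imply.

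This conclusion assumes that staff can tell the arms apart, and that the form and pathway do not already provide a uniform solicited record. If they do, the remedy is to say so in the protocol. The missing definitions and the clash over the end of participation are textual defects and need neither assumption. The primary endpoint and the sample size are not affected.

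**What to change.** - **Solicited record.** Add an item to the in-hospital list in section 3: a yes/no entry for each named event, completed in both arms with the existing twice-daily pain check (catheter site in the EDA arm only). State that the comparison of common events uses this record. If the hospital-stay form or the pathway already captures these events, cite it and say that it is completed identically in both arms.
- **Definitions.** Reconcile the cessation text in section 2 with the adverse-event text in section 3, so that the definitions cited by the first exist in the second. Their clinical content, and any threshold for blood pressure, are for the investigators to set.
- **Follow-up.** Reconcile the end of participation in section 2 with the outpatient visit in section 3. In the same edit, state whether the visit is timed from discharge, as its heading has it, or from surgery, as its text has it, and name the form on which it is recorded.

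The cost is a few tick boxes on an assessment already made twice a day and some short protocol edits. The downside is a small nursing burden and higher recorded event counts in both arms, since prompted enquiry finds more than spontaneous reporting.
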